### 2.3 Sample size calculation

This study is a randomized controlled trial aiming to compare the effects of TENS and taVNS in foraminoscopy. According to relevant research, with the VAS as the primary outcome indicator, the standard deviation of taVNS is 2.5, and that of TENS is 3.0. Calculated using PASS software, the minimum sample size required for each group is 121. Considering a dropout rate of 10%–15%, to ensure the statistical power and the reliability of the results, the final sample size of each group is adjusted to 136 people. Each subgroup was allocated 32 participants, and a total of 272 participants are recruited.

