**Methods:**

This investigation adopted a randomized, double-blind, controlled trial design. The participants were randomly divided into the TENS group and the taVNS group. Each group was further divided into three stimulation modes: continuous wave, intermittent wave, and dense–sparse wave. In each group, electrical stimulation was applied 30 min prior to surgery. The main parameters to be evaluated included the patients’ Visual Analogue Scale (VAS) scores, heart rate variability (HRV), bispectral index (BIS), Modified Observer’s Assessment of Alertness/Sedation Scale (MOAA/S) and the supplemental use of oliceridine fumarate during the surgery.

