### 2.2 Randomization and blinding

Patients are divided into two groups (TENS group and taVNS group) through a random number table generated by a computer. Each group is designed with a control group and three stimulation subgroups. A double–blind design is adopted, and neither the interveners (personnel implementing electrical stimulation interventions) nor the patients are aware of the grouping situation. They do not have access to the group allocation sequence, are not involved in randomization procedures, and do not participate in outcome assessments. To ensure effective blinding, all electrode pads will be covered with identical opaque adhesive membranes, with only the conductive contact point exposed. Additionally, electrode pads will be applied to both the auricular and acupoint regions in all participants, regardless of group allocation. As a result, the interveners will not know which site is actively receiving stimulation.

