## 3 Statistical analysis methods

### 3.1 Statistical methods for primary and secondary outcomes

This study will use SPSS 20.0 and PhysioZoo software for statistical analysis. The significance level of all statistical tests is set at α = 0.05, and two-sided tests are performed. For the differences in different intraoperative indicators such as pain score VAS, anesthesia depth BIS, and heart rate variability HRV between the trans-auricular vagus nerve stimulation group (taVNS group) and the transcutaneous peripheral nerve stimulation group (TENS group), an independent-samples *t*-test is first performed. If the data do not meet the normal distribution, the non-parametric test method Mann–Whitney U test will be used for comparison between the two groups. For the comparison between different subgroups (different stimulation modes) within each group, one-way analysis of variance will be performed to compare the differences in various indicators. If the data do not meet the assumptions of analysis of variance, the Kruskal–Wallis H test will be used as a non-parametric alternative method. At the same time, for multiple-measurement data, repeated-measures analysis of variance (Repeated Measures ANOVA) will be used to compare the changes of indicators at different time points within the same group. To further evaluate the impact of different influencing factors (such as stimulation mode) on intraoperative analgesia and sedation effects, multiple linear regression analysis will be used to help identify their relationships with various indicators.

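### Subgroups of 32 do not add up to the stated 136 per group and 272 in total; a secondary, minor point is that 136 covers 11% dropout, not the upper end of 10% to 15%

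*Protocol article*

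**What the plan says.** Section 2.3 (Sample size calculation) takes VAS as the primary outcome, with standard deviations given as follows: "the standard deviation of taVNS is 2.5, and that of TENS is 3.0". It reports that "the minimum sample size required for each group is 121". It then allows for a dropout rate of 10% to 15% and says that "the final sample size of each group is adjusted to 136 people". The section closes with the subgroup size and the total: "Each subgroup was allocated 32 participants, and a total of 272 participants are recruited".

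The number of subgroups comes from two other places. Section 2.2 (Randomization and blinding) says: "Each group is designed with a control group and three stimulation subgroups". Section 2.4.2 (Intervention description) lists the same four under the subdivision of each stimulation group: continuous wave, intermittent wave, dense-sparse wave, and a control with electrodes placed but not energised.

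Section 2.3 gives neither the VAS difference to be detected nor the power behind the 121. Section 3.1 fixes the test level: "The significance level of all statistical tests is set at α = 0.05, and two-sided tests are performed".

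**The concern.** Two consecutive sentences in section 2.3 give three counts: per subgroup, per group and overall. With the four subgroups per group described in sections 2.2 and 2.4.2, these counts should be linked by simple multiplication, and they are not. A reader cannot tell whether each waveform or control cell is to hold 32 or 34 participants, whether the control cell is larger than the others, or whether the trial will in fact randomise 256.

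This matters in two ways. The waveform comparisons within each group (one-way analysis of variance, section 3.1) rest on the cell sizes. And if the list were built on cells of 32, the group size would be 128 rather than 136, which uses up most of the allowance for dropout.

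The dropout allowance raises a smaller question of its own, namely whether 136 is enough across the whole of the stated 10% to 15% range.

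**Working it through.** **Inputs.** Two groups, each with one control and three stimulation modes (sections 2.2 and 2.4.2). From section 2.3: 32 per subgroup, 136 per group, 272 in total, minimum 121 per group, dropout 10% to 15%, SDs 2.5 and 3.0. From section 3.1: two-sided α = 0.05.

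**Step 1: the group total.** 2 × 136 = 272. This reproduces the stated total.

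**Step 2: the subgroup total.**
- Per group: 4 × 32 = 128, against 136 stated (8 short).
- Overall: 8 × 32 = 256, against 272 stated (16 short; 16/272 = 5.9%).
- Other counts of equal cells of 32 do not help: six cells (no controls) give 192, seven cells (one shared control) give 224, and 272/32 = 8.5 is not a whole number of cells.

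**Step 3: what would fit.**
- Equal cells: 136/4 = 34, and 8 × 34 = 272.
- Unequal cells: if 32 refers only to the three stimulation modes, the control holds 136 − 3 × 32 = 40 per group. The text gives no control size and no allocation ratio.

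**Step 4: dropout, from n / (1 − d) with n = 121.**

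| Dropout | Needed per group |
|---|---|
| 10% | 121/0.90 = 134.4, so 135 |
| 11% | 121/0.89 = 136.0, so 136 |
| 15% | 121/0.85 = 142.4, so 143 |

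The loss that 136 covers is 1 − 121/136 = 11.0%. The looser rule n × (1 + d) gives 121 × 1.15 = 139.2, so 140 at 15%, which still exceeds 136.

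Participants remaining per group:

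| Randomised per group | 10% loss | 15% loss | Loss at which 121 remain |
|---|---|---|---|
| 136 | 122.4 | 115.6 | 11.0% |
| 128 (cells of 32) | 115.2 | 108.8 | 5.5% |

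**Step 5: effect on power.** The difference and power behind 121 are not stated, so they have to be assumed. The normal approximation is n = (2.5² + 3.0²)(z₀.₉₇₅ + z_power)² / Δ², with 2.5² + 3.0² = 15.25.
- At 80% power and Δ = 1.0 it gives 119.7, so 120. A t-test with unequal variances has power of 79.8% at 120 and 80.1% at 121, so these assumptions reproduce 121.
- At 90% power, 121 would correspond to Δ of about 1.15.

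| Assumption behind 121 | 136 per group, 15% loss | 128 per group, 10% loss | 128 per group, 15% loss |
|---|---|---|---|
| 80% power, Δ about 1.0 | about 78% | about 78% | about 76% |
| 90% power, Δ about 1.15 | about 88–89% | about 88–89% | about 86–87% |

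**The case against.** The strongest reply is that 34 is not established as the intended number. Section 2.2 words the control separately from the three stimulation subgroups, and section 3.1 glosses subgroups as the stimulation modes. On that reading 32 applies to three cells, and a control of 40 gives exactly 136 and 272. This stands in part. It shows that 34 is the only answer for equal cells and not the only answer overall. It does not remove the defect: section 2.4.2 lists the control alongside the three modes, and no passage gives a control of 40 or says that allocation is unequal. Figure 1, the grouping flowchart, is not visible in the text reviewed and may carry numbers per arm. If it does, the text of section 2.3 should still agree with it.

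On dropout, the reply is that the plan gives a range and nowhere claims that 136 protects against 15%. The 11% that 136 covers lies inside the range, and 121 × 1.125 = 136.1 suggests simple inflation at the midpoint. That is fair, and it is why this part is minor. It remains true that the upper end of the plan's own range takes the number below its own minimum. The planned intention-to-treat analysis, with use of recent data from those who withdraw (sections 2.4.2.1.1 and 3.3), may also mean that not every dropout is lost to the analysis. The counts in the working treat every dropout as lost, as the plan's own inflation from 121 does.

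Two stronger readings are tempting and are not supported. A reader might infer that no allocation list can be built from these figures. In fact the two-group split of 136 and 136 is consistent, and only the division within each group is unclear. A reader might also infer that the Abstract conflicts with the body, because it says "Each group was further divided into three stimulation modes" and names no control. An unenergised control is not a stimulation mode, and leaving it out of an abstract is ordinary condensation.

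**Conclusion.** The subgroup size in section 2.3 is inconsistent with the group size and the total, given the four subgroups per group in sections 2.2 and 2.4.2. The gap is 8 per group and 16 overall. This rests on the document's own counts and on no outside assumption. Which figure was intended cannot be settled from the text: it is 34 if cells are equal, 32 with a larger control if they are not, or 32 throughout if the true total is 256. In the last case the allowance for dropout falls to 5.5%, below the stated range.

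The dropout point holds only in a limited form: 136 covers the lower end of the range, up to 11%, and leaves about 116 at 15%. The cost is about 2 points of power (about 78% against 80%) if the difference was 1.0 and the power 80%, and of similar order (88–89% against 90%) if the difference was about 1.15 and the power 90%. Both pairs are assumptions. On its own this would not need more than a sentence.

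**What to change.** Reconcile section 2.3 with the allocation list, keeping 136 per group and 272 in total:
- If cells are equal, replace 32 with 34 per subgroup (4 × 34 = 136; 8 × 34 = 272).
- If the control cell is meant to be larger, for example 40 with three cells of 32, say so and give the allocation ratio.
- If the list really uses eight cells of 32, restate the size as 128 per group and 256 in total, and say that this covers 5.5% loss from 121.

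In the same section, say that 136 allows for 11% loss, or say that the minimum of 121 is not kept at 15%. For information, keeping 121 at 15% would take 143 per group, or 144 (36 per subgroup, 288 in total) with four equal cells. The small power loss does not by itself call for that increase.

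The cost is a text correction and a check of the randomisation list. Keeping 136 and 272 needs no additional participants. No change to the Abstract is needed.

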### 2.4 Intervention measures

#### 2.4.1 Explanation for the choice of comparators

Previous studies have shown that both TENS and taVNS have certain effects on pain regulation. However, there are few studies comparing the differences in the efficacy of the two, and the electrical stimulation parameters have not been made public. Therefore, this study aims to compare the differences in the efficacy of the two and obtain the appropriate electrical stimulation parameters for foraminoscopy.

#### 2.4.2 Intervention description

Based on a systematic review and related studies (23), each group receives 30-min corresponding stimulation or placebo intervention before surgery. The current intensity is adjusted to the maximum tolerance of the patient, the pulse width is fixed at 200 μs, and the frequency is fixed at 30 Hz. When patients with severe pain cannot tolerate it, oliceridine fumarate injection is supplemented to the subjects. The supplementary standard is: a single dose of 0.35 mg–0.50 mg, intravenous injection, and the dosing interval is not less than 6 min.

•TENS Group: Electrodes are placed at the bilateral Neiguan and Hegu acupoints of the subjects. Hegu (LI4): Located on the dorsum of the hand, between the 1st and 2nd metacarpal bones, at the midpoint of the radial side of the second metacarpal bone. Neiguan (PC6): Located on the palmar aspect of the forearm, 2 cun proximal to the transverse wrist crease, between the tendons of the palmaris longus and the flexor carpi radialis muscles.•TaVNS Group: Electrodes are placed at the bilateral tragus of the subjects.

Each stimulation group was further subdivided into following stimulation modes:

•Continuous Wave Group: Given 30-min continuous electrical stimulation.•Intermittent Wave Group: Subjects receive 30-min intermittent electrical stimulation (stimulate once every 15 s, with an interval of 5 s).•Dense-Sparse Wave Group: Subjects receive 30-min variable–frequency electrical stimulation (sparse wave 6 Hz, dense wave 30 Hz).•Control Group: Electrode patches are placed but not energized, making the patients psychologically believe that they have received stimulation.

The experimental process is shown in Figure 1.

**FIGURE 1 F1:**
[figure not shown]
Flowchart of experimental intervention grouping.

##### 2.4.2.1 Observation indicators

Record the changes of corresponding indicators at different time points:

•Time 1: 5 min after the patient enters the operating room, before electrical stimulation.•Time 2: Before the operation, 30 min after the electrical stimulation upon entering the room.•Time 3: Immediately at the start of the operation.•Time 4: 0.5 h after the start of the operation.•Time 5: 1.0 h after the start of the operation.•Time 6: 1.5 h after the start of the operation.•Time 7: 2.0 h after the start of the operation.•Time 8: At the end of the operation.

###### 2.4.2.1.1 Criteria for discontinuing or modifying allocated interventions

If a subject withdraws from the experiment midway or is not satisfied with the analgesic effect, the recent data will be calculated for analysis according to the intention–to–treat principle. Conventional drugs will be used for analgesia and sedation management, and the reason for withdrawing from the study will be recorded.

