##### 2.1.4.3 Withdrawal criteria

•Deviation from the assigned anesthesia protocol.•Occurrence of any serious adverse event.•Intraoperative administration of heart rate-altering medications (e.g., atropine).•Failure to complete all required monitoring procedures.

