###### 2.4.2.1.3 Relevant concomitant care permitted or prohibited during the trial

During the entire trial, subjects are required not to use any other analgesic measures or drugs, as this may affect the outcome.

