### 3.3 Methods in analysis to handle protocol non–adherence and any statistical methods to handle missing data

Intention-to-treat analysis will be used, and missing data will be appropriately processed in accordance with established guidelines.

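### A single undefined recent-data rule covers both withdrawal and dissatisfaction with analgesia, and it can bias the VAS comparison in either direction

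*Protocol article*

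**What the plan says.** Section 2.4.2.1.1 of the protocol article gives the rule: "If a subject withdraws from the experiment midway or is not satisfied with the analgesic effect, the recent data will be calculated for analysis", and attributes it to the intention-to-treat principle. It continues: "Conventional drugs will be used for analgesia and sedation management, and the reason for withdrawing from the study will be recorded". The two events, leaving the trial and being dissatisfied with pain relief, are handled together, and the follow-on sentence treats both as withdrawal.

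Other sections bear on the same patients:

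- Section 2.4.2, on timing of the intervention: "each group receives 30-min corresponding stimulation or placebo intervention before surgery".
- Section 2.4.2.1 lists eight assessment times, the last being "Time 8: At the end of the operation". Table 1 schedules VAS at all eight.
- Section 3.3, on missing data: "Intention-to-treat analysis will be used, and missing data will be appropriately processed in accordance with established guidelines".
- Section 2.1.4.3 includes among the withdrawal criteria: "Deviation from the assigned anesthesia protocol".
- Section 2.1.4.2 excludes patients who have a severe adverse reaction during surgery that ends the operation or changes the anaesthetic method.
- Section 2.4.2.1.3, on concomitant care: "subjects are required not to use any other analgesic measures or drugs, as this may affect the outcome".

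**The concern.** The rule is triggered by something close to the outcome itself. VAS is a primary indicator (section 2.5.1) and the outcome used for sizing (section 2.3). A patient dissatisfied with analgesia is telling the trial about pain.

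Such a patient has also, in the usual case, already received the whole allocated intervention, because stimulation ends before the operation starts. There is no allocated treatment left to discontinue. The patient is still under monitoring, and VAS is scheduled to the end of surgery. Fixing the analysis on data from around the event gives up information that can generally still be collected. Intention-to-treat means analysing patients as randomised; it does not by itself justify using an older score in place of a later one.

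Section 3.5 expects a stronger analgesic effect and less supplementary oliceridine with taVNS than with TENS. If that is right, dissatisfaction could well differ between arms, and with it the number of truncated or substituted scores. Part of the VAS contrast would then reflect when patients met the rule and not how much pain they had.

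**Working it through.** **1. What the rule can mean.**

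| Reading | Consequence for later VAS |
|---|---|
| Last available value carried forward (most natural) | Later time points hold an older score |
| Only data up to the event are used | Later scores are absent from the analysis |
| Latest data actually collected, to the end of surgery, in the randomised arm | Nothing is lost |

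The third reading fits the intention-to-treat label, but it sits poorly with a sentence that goes on to record a reason for withdrawing. The first two both lose later scores.

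**2. Direction under carry-forward.** Let p be the proportion affected in an arm and g the true later score minus the carried score. At a time point after the event:

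shift in (taVNS − TENS) = p(TENS) × g(TENS) − p(taVNS) × g(taVNS)

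- Carried score from a quieter period: g is positive and later pain is understated.
- Carried score is the high one that prompted the complaint, and conventional drugs then relieve the pain: g is negative and later pain is overstated.

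The text does not settle which applies, so the sign is open. With equal p and equal g in both arms the shift is zero.

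**3. Scale: the plan's own figure.** Section 2.3 gives SDs of 2.5 (taVNS) and 3.0 (TENS) and 121 per group. Section 3.1 gives two-sided α = 0.05. The article states neither the VAS difference nor the power, so 121 cannot be reproduced from its inputs alone. Assuming 80% power:

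- SE = √((2.5² + 3.0²)/121) = √(15.25/121) = 0.355
- Detectable difference = (1.960 + 0.842) × 0.355 = 0.99, about 1.0
- In reverse, a difference of 1.0 at 80% power needs 120 per group by the normal approximation. An unequal-variance t-test at 121 has power 0.801.
- At 90% power the difference implied by 121 would be 1.15.

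**4. Illustration.** The documents give no rates of dissatisfaction and no score changes, so p and g are assumptions, with the same g in both arms.

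| taVNS affected | TENS affected | Size of gap | Size of shift |
|---|---|---|---|
| 10% | 10% | any | 0 |
| 10% | 20% | 2 | (0.20 − 0.10) × 2 = 0.2 |
| 10% | 20% | 4 | (0.20 − 0.10) × 4 = 0.4 |
| 10% | 30% | 3 | (0.30 − 0.10) × 3 = 0.6 |

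A shift of 0.2 to 0.4 is 20% to 40% of a detectable difference of 1.0. With SE 0.355 and no true difference, it raises the two-sided rejection rate from 0.05 to 0.087 (shift 0.2) or 0.203 (shift 0.4). Working against a true difference of 1.0, it lowers power from 0.80 to 0.62 or 0.39.

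**5. Precision.** Carried-forward values analysed as if observed would also misstate the standard errors, because a copied score carries no new information.

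**The case against.** The strongest reply is that carry-forward is an inference. The article does not say that a score is carried forward, that it replaces later ones, or that VAS recording stops. Table 1 schedules VAS to the end of surgery with no exemption. That stands, and it is why the point is conditional. A reader might infer that the rule substitutes a score from before analgesia failed and so understates pain. The document does not say this, and the latest score could equally be the high one at failure.

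A second reply is that sections 2.4.2.1.1 and 3.3 do not truly conflict: one is specific, the other general, and the detail may lie in an analysis plan not shown. That largely stands. The generality of section 3.3 is no finding. The point rests on the rule that section 2.4.2.1.1 does state, which a later document would have to undo.

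Third, later scores may not always be obtainable: a patient given conventional sedation may be unable to rate pain. Some of the same patients may also leave by other routes: the withdrawal criterion on departing from the anaesthesia protocol or, after a severe adverse reaction, the exclusion criterion. This stands. Later scores are generally, not always, available.

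Fourth, the illustration is generous. Rates of 10% and 20% average 15%, the top of the dropout range in section 2.3. Supplementary oliceridine (section 2.4.2) may leave only a residual group under this rule, and the shift applies only at time points after the event. All fair; the figures show scale and predict nothing.

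**Conclusion.** The concern holds in a conditional form. One undefined rule merges an outcome-related event with true withdrawal and, on its two most likely readings, loses VAS scores that are generally still obtainable. If dissatisfaction differs between arms in frequency or timing, the VAS comparison can be biased, in a direction that cannot be fixed from the text. The illustrated size is 0.2 to 0.4 points against a detectable difference of about 1.0. That rests on assumed rates of 10% and 20%, an assumed gap of 2 to 4 points common to both arms, and assumed 80% power.

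A reader might go further and conclude that the trial's VAS result is bound to be biased, or biased towards one arm. The documents do not support that. This should be fixed; confidence is moderate, because the meaning of the key term is inferred.

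**What to change.** In section 2.4.2.1.1, for data collection and analysis only:

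1. Separate dissatisfaction with analgesia from withdrawal of consent to data collection.
2. After dissatisfaction, continue the scheduled VAS assessments wherever the patient can give a score, and analyse the observed values in the randomised arm.
3. Record the time of any switch to conventional drugs and report switches by arm.
4. For values truly unobserved, replace the recent-data rule with a likelihood-based repeated-measures model or multiple imputation, with a sensitivity analysis.

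State the same rule in section 3.3. Reconcile it with the exclusion criteria (2.1.4.2) and withdrawal criteria (2.1.4.3), which may remove the same patients. Also reconcile it with section 2.4.2.1.3, whose bar on other analgesics does not square with the conventional drugs foreseen in 2.4.2.1.1. Which clinical rule should apply is for the investigators.

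The cost is mainly protocol wording; the assessments are already scheduled, so no visits are added. The sample size is unchanged. A small downside is that scores after a switch include the effect of the conventional drugs, so the VAS result must be read alongside the switches by arm. The change should be made before data collection where possible, because intraoperative scores that were not recorded cannot be recovered.
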